### Sample size

We plan to study the effects of daily AIH alone and with WALK in N = 85 persons with subacute SCI. The sample size is a sum of participants who enroll in Aims 1 and 2. We established a Consolidated Standard of Reporting Trials CONSORT flow diagram to summarize our trial enrollment, intervention, allocation, follow-up, and analyses [24].

For Aim 1, our sample size computation focused on interventions: daily AIH versus daily SHAM. Data from our previous randomized clinical trial that examined the effects of daily AIH (vs daily SHAM) on walking speed in persons with chronic SCI showed an effect size of 0.84 at our final follow-up. Using this value, our estimated sample size for this aim is N = 34 participants (includes 12% attrition rate), for a sensitive non-parametric comparison of means between interventions to detect a significant difference at power > 0.8 (f = 0.6, F_1,39_ = 4.6; ρ = 0.4, α = .05).

For Aim 2, our sample size computation focused on interventions: daily AIH + WALK versus daily SHAM+WALK. Data from our previous randomized clinical trial that examined the effects of daily AIH + WALK (vs daily SHAM+WALK) on walking endurance (6MWT) in persons with chronic SCI showed a significant increase of total distance walked (131 ± 100 m). Our preliminary data of the effects of daily AIH alone showed an increase of 23.9 ± 18.0 m on the 6MWT. Using these values and under the hypothesis of an additive effect of daily AIH + WALK (vs daily SHAM+WALK, WALK), we anticipate the difference in change of walking distance between daily AIH + WALK vs daily SHAM+WALK or vs WALK will be approximately 100 m. Hence, our estimated sample size for this aim is N = 51 participants (includes 12% attrition rate), for a sensitive repeated measures ANOVA comparing interventions across 3 time points, using a pooled standard deviation of 90 m, to detect a significant difference at power > 0.8 (f = 0.6, F_1,38_ = 4.4; ρ = 0.4, α = .05).

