#### Randomization and stratification

We stratify eligible participants into either an ambulatory or a non-ambulatory group based on their initial walking function. The ambulatory group includes eligible participants who successfully complete one of the following without human assistance: TUG, 10MWT, or 6MWT without human assistance. Participants enrolled in the non-ambulatory group are unable to complete any of these assessments at initial screening. Prior to enrollment of the first study participant, a research statistician generated the balanced, randomization scheme for treatment allocation in both non-ambulatory and ambulatory groups using the R Statistical Package [29]. Using this scheme, the clinical coordinator assigns each participant to their respective treatment group using their alphanumeric identifier.

Although we inform participants about their group, we blind them to the treatment they receive (i.e. daily AIH or daily SHAM). The clinical raters, trainers, and data analysts are also unaware of the treatment that each participant receives during after the trial. We plan to rigorously quantify our blinding methods. Participants guess the breathing intervention received at the end of each treatment day and indicate guess confidence using a Likert scale [30, 31]. Using a contingency table and Fischer’s Exact Test, we will determine if the probability of correct guessing is different from chance. Using multivariate logistic regressions, we also will assess factors that may influence guessing (e.g., adverse events, perceived effects, and sensorimotor changes).

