**Fig. 1 Fig1:**
[figure not shown]
Timeline of intervention and outcome measurements

Participants receive 10 treatment sessions of daily AIH or daily SHAM. A single AIH session consists of 15, 90s episodes of breathing at a fraction of inspired oxygen (FiO_2_) of 0.10 ± 0.02 with 60s intervals of 0.21 ± 0.02 FiO_2_ (room air). While a single daily SHAM session consists of 15, 90s episodes of 0.21 ± 0.02 FiO_2_ with 60s intervals of 0.21 ± 0.02 FiO_2_ (room air). We provide the treatments via a custom air delivery system; see [10, 23, 32–34] for details. In brief, the delivery system directs a known air mixture from either a pressure-swing absorption (PSA) system [HYP-123; Hypoxico Inc., USA] or a blower source to the non-rebreather facemask. For safety, oxygen concentration within the breathing circuit is continuously monitored [OM-25RME; Maxtec Inc]. Additionally, we continuously monitor blood oxygen saturation (SpO_2_) and heart rate (HR) at 1-s intervals, and blood pressure (BP) every 5th breathing interval using a MASIMO system [MASIMO rainbow SET, Irvine, CA].
C.Walking practice

Walking practice sessions immediately follow (within 10 min) the breathing intervention and last for 60 min. Walking practice involves intensive training in walking-related functional tasks using a skill-based training approach. Recent studies found skill-based walking practice is more consistent with community walking, providing meaningful gains in walking function after neurologic injury [35–37]. Task-based walking practice replicates environmental challenges encountered during real-world walking [36] and corresponds to gains in walking balance, speed, and endurance that can be measured using the timed-up and go (TUG), 10-m walk test (10MWT), and 6-min walk test (6MWT), respectively [37]. The walking practice incorporates activities to develop skills in 5 walking-related task domains: 1) walking balance (e.g., walking on different surfaces), 2) skilled walking (e.g., negotiating obstacles), 3) walking with a secondary task (e.g., walking and carrying object), 4) endurance, and 5) speed [37].

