### Statistical analysis

To advance our understanding and the applicability of daily AIH-induced walking recovery, we plan to test three sub-hypotheses using parametric and non-parametric statistical inferencing. Statistical significance corresponds to a p-value less than 0.05.

#### Hypothesis 1

Daily AIH improves walking recovery in persons with subacute SCI initially unable to walk as compared to daily SHAM. We plan to quantify the success of completing walking skills using our primary outcome measures (i.e., TUG, 10MWT, and 6MWT) by a recovery score of 0–3. We predict that the number of walking skills recovered will be greater for participants receiving daily AIH vs daily SHAM, indicating improved walking ability. We will use a Friedman two-way (factor 1 = intervention: daily AIH, daily SHAM; factor 2 = time: baseline, mid-test, post-test, and follow-ups) repeated measures analysis of variance (ANOVA) by ranks to compare walking recovery between and within groups. If there are significant differences, we plan post-hoc tests for pairwise comparisons [50]. We also anticipate that improvement in walking recovery will correlate with improved SCI-FAI, WISCI and LEMS scores, suggesting clinical relevance of daily AIH as an intervention across various SCI impairment levels.

#### Hypothesis 2

Daily AIH + WALK improves walking ability in ambulatory persons with subacute SCI as compared to daily SHAM+WALK and WALK. We predict a decrease in 10MWT and TUG time and an increase in 6MWT distance relative to baseline following dAIH+WALK (vs. dSHAM+WALK, WALK). We will test three related sub-hypotheses using a linear mixed model with fixed effects [51]. We will use intervention (daily AIH + WALK, daily SHAM+WALK, WALK) and time (day) as the fixed main effects, with subject as random effect, while scores for TUG (time), 10MWT (time), and 6MWT (distance) will be considered as repeated measures. Differences from baseline scores will be compared between and within interventions at mid-test, post-test, and follow-ups. If ANOVAs reveal significant differences, we will use the Tukey-Kramer post-hoc test to identify pairwise differences. If baseline measures are significantly different between intervention groups, we plan to use an analysis of co-variance (ANCOVA) to analyze these data.

#### Hypothesis 3

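### The blinding check names Fisher's exact test and plain logistic regressions for ten guesses per participant without naming the unit of analysis; if person-days are pooled, the 5% level is lost

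*Protocol article*

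**What the plan says.** Under Randomization and stratification, the article promises to quantify blinding rigorously. The data are described as follows: "Participants guess the breathing intervention received at the end of each treatment day and indicate guess confidence using a Likert scale". Under Intervention (Breathing treatment), "Participants receive 10 treatment sessions of daily AIH or daily SHAM", so a participant in a breathing arm who completes treatment supplies ten guesses.

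The analysis follows directly: from a contingency table and Fisher's exact test, "we will determine if the probability of correct guessing is different from chance". Then: "Using multivariate logistic regressions, we also will assess factors that may influence guessing". The section does not say whether the table holds person-days, one table per day, or one guess per person, and it mentions no participant effect. The only error level given is the general one under Statistical analysis: "Statistical significance corresponds to a p-value less than 0.05".

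For the efficacy outcomes, by contrast, the Statistical analysis section does handle repetition. Hypothesis 1 has a repeated-measures analysis by ranks, and Hypothesis 2 a mixed model with subject as a random effect.

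**The concern.** Each participant in a breathing arm receives the same gas mixture on all ten days, so someone who suspects hypoxia on one day will tend to suspect it again. Ten guesses from one person then carry much less information than ten guesses from ten people. Fisher's reference distribution ignores this. A few persistent guessers who happen to fall unevenly across the arms can produce a small p-value although nobody has detected their allocation.

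The result matters for interpretation. The walking tests are performed at the participant's fastest comfortable speed and so depend on effort. The Safety precautions section lists lightheadedness and dizziness as possible effects of low oxygen, so unblinding is a real possibility. A false alarm would unfairly weaken confidence in an AIH versus SHAM difference. A low-powered test read as reassurance would unfairly strengthen it.

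**Working it through.** **Inputs from the article.** Ten guesses per person. Level 0.05, taken as two-sided. For Aim 1, "our estimated sample size for this aim is N = 34 participants (includes 12% attrition rate"), which is 34/2 = 17 per arm if balanced. For Aim 2, "our estimated sample size for this aim is N = 51 participants (includes 12% attrition rate"), which is 51/3 = 17 per arm, with two of the three arms receiving a breathing intervention. After 12% attrition, 17 × 0.88 ≈ 15 per arm, or about 30 per arm if both aims are combined.

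**Input not in the article.** The within-person correlation of guesses (ICC) is an assumption, and a range of 0 to 0.9 is shown.

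The article states no size or power for this check, so there is no figure to reproduce.

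**Step 1: pooled person-days, by formula.** With ten guesses per person the variance is multiplied by 1 + 9·ICC. The true size of a nominal 5% test is then about 2·[1 − Φ(1.96/√(1 + 9·ICC))]. At ICC 0.2, for example, 1 + 9 × 0.2 = 2.8, √2.8 = 1.673, 1.96/1.673 = 1.171, and the size is 24.1%.

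**Step 2: the same by simulation.** Perfect blinding, beta-binomial guesses, two-sided Fisher on the pooled table, 15 to 34 per arm, 2,000 trials per cell (Monte Carlo error about 1 point):

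| ICC (observed scale) | Formula | Simulated pooled Fisher |
|---|---|---|
| 0 | 5.0% | 3.6–4.6% |
| 0.1 | 15.5% | 14–15% |
| 0.2 | 24.1% | 22–26% |
| 0.3 | 30.8% | 28–30% |
| 0.5 | 40.3% | 38–40% |
| 0.7 | 46.8% | 44–47% |
| 0.9 | 51.6% | 49–53% |

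Solving the formula for 20% and 40% gives ICC 0.15 and 0.49.

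**Step 3: a second model.** A normal random intercept on the logit scale with SD 1, 2 and 3 has latent ICC SD²/(SD² + π²/3) = 0.23, 0.55 and 0.73. Over repeated runs with 15 to 34 per arm, pooled Fisher rejected in 19–22%, 33–37% and 39–42%. The latent and observed ICCs are different scales, but both models lead to about 20–40%.

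**Step 4: direction.** With equal arms and perfect blinding the two tails are symmetric. About half of the rejections, 10–20% of trials, therefore have correct guessing above chance. The rest have it below chance.

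**Step 5: other readings of the text.**
- One pre-chosen day, one guess per person: size 1–3%, so no inflation.
- Ten daily tests, any one significant: 15–25% at ICC 0, falling to 5–8% at ICC 0.9. This is multiplicity, not clustering, and the article does not say that one significant day would count as failure.
- Participant-level t test on each person's guess proportion: 4–6% at every ICC tried.

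**Step 6: power with one guess per person.** If 70% guess correctly in each arm, 70% guess AIH in the AIH arm and 30% in the SHAM arm. Exact enumeration of two-sided Fisher gives power 0.43 at 15 per arm, 0.55 at 17 and 0.84 at 30 (both aims combined). At 15 per arm the test misses this degree of unblinding 57% of the time.

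**The case against.** The strongest reply is that the article says when guesses are collected and which test is used, but never that all ten enter one table. A condensed article may leave the unit of analysis, and the regression's random effects, to the full protocol or analysis plan. If one guess per person is meant, the test is valid. This stands: pooling is a plausible reading, not a stated plan.

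It follows that a reader should not infer that this trial's blinding check, as planned, will report broken blinding in 20–40% of perfectly blinded trials. That inference needs pooling, which the text does not state, and a correlation that the text does not give. It would also count rejections in which participants guessed worse than chance.

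Further points also stand. Low power is a problem within one aim and much less so if the aims are combined. The article nowhere says that a non-significant result will be taken as proof of blinding. No decision rule or efficacy test uses the result.

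What the reply does not remove is the mismatch in what is written. The only guess data described are repeated within person, and the only methods named treat observations as independent. The article specifies repeated-measures methods for the efficacy outcomes but not here.

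**Conclusion.** The point holds conditionally. The named test does not fit the guess data as described unless the ten guesses are first reduced to one value per participant, and the article does not say that they are. If person-days are pooled, the false-rejection rate is about 20–40% for an observed-scale ICC of about 0.15–0.5, and about 4% to 53% over ICC 0 to 0.9. Even at ICC 0.1 it is about three times the nominal level. Logistic regressions fitted to person-days without a participant term would make the same independence assumption.

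The documents do not support calling the planned check invalid outright. The finding is that the unit must be fixed, and that the most direct reading of the text loses error control. The consequence is limited to how far the blinding claim can be trusted. It is worth correcting before the guesses are analysed.

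**What to change.** - State that the participant is the unit of analysis. Compare AIH and SHAM on each participant's proportion of 'AIH' guesses over the ten days, by a permutation or t test, separately for Aims 1 and 2.
- Report an arm-specific blinding index (Bang) with a 95% confidence interval at pre-named days, such as day 1 and day 10.
- Judge blinding from the estimate and its interval, not from p > 0.05.
- Fit the logistic regressions on guessing with a participant random effect or by GEE.

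The cost is a change of wording. The guesses are already being collected and no efficacy analysis changes. The drawback is wider intervals for the blinding result, which reflect the number of participants rather than the number of guesses.

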### Intervention

A.Duration

All participants enroll in 15 sessions at one of two site laboratories (1 baseline + 10 treatment days + 3 follow-up visits). Baseline (BL) evaluation occurs prior to the first day of intervention. Participants in each intervention group complete a total of ten days of intervention and 3 follow-up sessions (Fig. 1). If participants miss a treatment session, we do not conduct further assessments and exclude their data from analyses. However, if participants miss an assessment session, we record their data as “missing” at that time point.
B.Breathing treatment

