### Safety precautions

To ensure participant safety, we implement the following precautions:
A.*Protection against low oxygen risks during breathing sessions:* As moderate reductions in inspired oxygen may cause lightheadedness, dizziness, reduced vision, and/or euphoria, we continuously monitor SpO_2_, HR, and BP of all participants before, during, and after treatment and/or assessment sessions. If during a daily AIH treatment session a participant’s SpO_2_ levels fall below 70%, our AIH-delivery system is programmed to immediately switch from hypoxia to normal oxygen delivery (i.e. FiO2 = 0.21 O_2_) until the participant’s SpO_2_ levels re-saturate above 90%. Additionally, if participants exhibit any signs of lightheadedness, dizziness, reduced vision, and/or euphoria during a treatment session, we will immediately administer room air with our automated delivery system and the onsite study physician will conduct a clinical examination to assess if the participant should continue with treatment or terminate the session. Participants are able to discontinue treatment at any time for any reason.B.*Protection against fall risk during walking assessments and training:* We record each participant’s fall history and document any adverse events that may occur during their training or assessment visits. To ensure safety for all walking assessments, we allow participants to use an assistive device (AD) (e.g. cane, walker, crutches etc.) depending on their level of comfort and ambulatory status, while the assessing therapist and research assistants walk beside them. We also ensure that participants use the same AD for all assessments. To ensure participant safety during all walking-training sessions, the training physical therapist constantly monitors the participant and uses a gait belt if considered clinically necessary.C.*Protection against fatigue risk:* For all breathing sessions, we position participants in a comfortable seated or reclining position to minimize discomfort. During walking practice training, we ensure participants take seated or standing rest breaks every 5–10 min (or when requested) and between different modules. We resume training only after participants provide verbal confirmation that they are ready to continue. For all assessments, we continuously monitor participants for fatigue and balance instability, and ensure that they take frequent rest breaks (2–5 min) between different assessment tests.D.*Protection against cardiopulmonary risk:* The assigned physical therapist (with help from a research assistant) monitors cardiopulmonary vitals (i.e. HR, BP, and SpO_2_) pre and post all assessment and treatment sessions (breathing and walking training). If a participant reports any discomfort, the on-site clinician will stop the assessment/training session for a seated/standing break (depending on participant preferences) and monitor vitals to determine if the participant’s condition is stable enough to continue after a rest period or to terminate the session altogether. The onsite clinician can also immediately withdraw participants from the study in case of serious medical issues that may arise during treatment or assessment; for example, signs of autonomic dysreflexia, rapid change in heart rate or systolic blood pressure, diaphoresis, severe headache or dizziness. All clinical and research staff members are trained to provide First Aid and CPR in case of emergency. Additionally, if a participant gets ill or injured from being in our study, a medical team (present on site for all sessions) is available to attend to the participant. Participants can return to continuing the study only after they have received medical clearance from our study physician.

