Pain severity: Using the five-point Wong-Baker FACES scale of 0 (no pain) to 5 (extreme pain) [44, 45].Spasticity: Using the Spinal Cord Assessment Tool for Spastic Reflexes (SCATS) [46], and the cumulative sum of three SCATS subscales: clonus (0 = no spasticity; 3 = severe), flexor (0 = no spasticity; 3 = severe), and extensor (0 = no spasticity; 3 = severe); and spasms using the Penn Spasm Frequency Scale (PSFS) [47].Blood pressure: At all pre-post treatment/assessment and follow-up time points. For each participant we specifically record hypertension incident rate, i.e. number of hypertensive events divided by units of person-measures (the sum of the total number of BP measurements), which accounts for the total number of chances for detecting a hypertensive event and for measurements not made due to dropout or a disqualifying adverse event [48]. We will also compute relative risk for participants within each group, i.e. hypertension incidence rate in the daily AIH subgroup over that in the daily SHAM and/or WALK groups [49], respectively, with a relative risk of one indicating no association between systemic hypertension incidence with interventions.Autonomic dysreflexia incident rate i.e. number of autonomic dysreflexia events divided by the total person-time (number of study days completed by each participant) to account for the total number of chances for detecting autonomic dysreflexia for days not measured due to dropout or a disqualifying adverse event [48]. We also compute relative risk within each group, as autonomic dysreflexia incidence rate in the daily AIH group over the incidence rate in the daily SHAM and WALK groups, respectively [49].

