Daily AIH ± WALK does not induce maladaptive changes (spasticity, pain, systemic hypertension, autonomic dysreflexia) in persons with subacute SCI. First, we predict no difference in SCATS following daily AIH ± WALK as compared to daily SHAM±WALK or WALK. We also predict no difference in the changes in FACES scores between interventions. We anticipate daily AIH alone or combined with walking practice will not elicit greater incidence of systemic hypertension in persons with subacute SCI. To test this hypothesis, we will compare the incidence rates of hypertension between interventions (daily AIH, daily AIH + WALK, daily SHAM+WALK, WALK) using Relative Risk [49, 52]. A Relative Risk of one will indicate no association between systemic hypertension and interventions. Using the 95% confidence interval of the Relative Risk [49], we will determine if there is a statistically significant association between interventions. We predict the relative risk of hypertension comparing daily AIH vs. daily SHAM, daily AIH + WALK vs. daily SHAM+WALK, and daily AIH + WALK vs. WALK are not different. We also predict the incidences of autonomic dysreflexia comparing daily AIH vs. daily SHAM, daily AIH + WALK vs. daily SHAM+WALK, and daily AIH + WALK vs. WALK are not different.

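### One missed treatment session ends assessment and removes the participant's data: a post-randomisation exclusion that can bias the comparison and conflicts with the protocol's own safety rates

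*Protocol article*

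**What the plan says.** Under Intervention (Duration) the protocol article sets the schedule: "Participants in each intervention group complete a total of ten days of intervention and 3 follow-up sessions". It then gives the rule: "If participants miss a treatment session, we do not conduct further assessments and exclude their data from analyses". No cause is excepted. A missed assessment is handled differently: "if participants miss an assessment session, we record their data as “missing” at that time point".

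Four other places bear on this:

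- **Safety precautions** names lightheadedness, dizziness, reduced vision and euphoria as possible effects of reduced oxygen, and allows a session to be terminated. It adds: "The onsite clinician can also immediately withdraw participants from the study in case of serious medical issues that may arise during treatment or assessment". The examples include signs of autonomic dysreflexia and a rapid change in heart rate or systolic pressure. On illness or injury it says: "Participants can return to continuing the study only after they have received medical clearance from our study physician".
- **Outcome measures** defines the hypertension rate per blood pressure measurement, so that it accounts "for measurements not made due to dropout or a disqualifying adverse event". The autonomic dysreflexia rate, per study day completed, has a parallel provision. Pain (FACES) and spasticity (SCATS, PSFS) have none.
- **Statistical analysis, Hypothesis 3** states: "Daily AIH ± WALK does not induce maladaptive changes (spasticity, pain, systemic hypertension, autonomic dysreflexia) in persons with subacute SCI".
- **Sample size** gives 34 participants for Aim 1 and 51 for Aim 2, each of which "includes 12% attrition rate".

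Nothing in the article provides for analysing everyone as randomised.

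**The concern.** Attendance at ten sessions is observed only after allocation, and allocation can affect it. Only some arms breathe low oxygen, and only the Aim 2 arms walk for 60 minutes afterwards. Keeping only those who attended every session compares selected subsets, which need not be alike even though the randomised groups were. Blinded raters do not protect against this, because the selection lies in who is left to be rated.

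Half of the rule concerns conduct. Stopping assessments means that the outcomes are never collected, so an analysis plan written later could restore earlier data but not visits that did not take place.

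For the safety aim, two parts of the article give different answers on whether a person who stops because of an adverse event is counted.

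**Working it through.** **1. The plan's own figures.** 34 + 51 = 85 over five arms is 17 per arm (equal arms assumed). With 12% attrition, 17 × 0.88 = 15.0 per arm. For Aim 2 (difference 100 m, SD 90 m, two-sided 0.05 assumed), pairwise power at 15 per arm is Φ(100/(90 × √(2/15)) − 1.96) = Φ(3.04 − 1.96) = 0.86, or 0.84 by noncentral t. This agrees with the stated power above 0.8, and 45/0.88 = 51.1 agrees with 51. The 34 for Aim 1 reproduces only under a chosen repeated-measures variant; nothing below depends on it.

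**2. How many the rule could exclude.** The article gives no miss rate. Assume that each session is missed independently with the same probability p for everyone. Then P(at least one miss in ten) = 1 − (1 − p)^10. Setting this to 0.12 gives p = 1 − 0.88^0.1 = 1.27%.

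| p per session (assumed) | Excluded | Left of 34 | Left of 51 | Aim 2 pairwise power (normal) |
|---|---|---|---|---|
| 1% | 9.6% | 30.7 | 46.1 | 0.87 |
| 2% | 18.3% | 27.8 | 41.7 | 0.83 |
| 3% | 26.3% | 25.1 | 37.6 | 0.79 |
| 5% | 40.1% | 20.4 | 30.5 | 0.71 |

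These losses come before any ordinary dropout over the 12-month follow-up, which the same 12% must also cover.

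**3. What it could do to the Aim 2 contrast.** Assume no true effect and SD 90 m. Let a latent tendency to miss sessions have correlation r with a poor outcome, and let a fraction q of an arm be excluded. The retained mean in that arm rises by r × 90 × φ(z_q)/(1 − q), where z_q is the normal quantile of q. The bias in the contrast is the difference between arms.

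- 12% v 12%, same r: 0 m.
- 18% (AIH) v 6% (control): 90 × (0.320 − 0.127) × r = 17.4r, which is +5.2 m at r = 0.3 and +8.7 m at r = 0.5.
- 24% v 6%: 90 × (0.409 − 0.127) × r = 25.4r, which is +7.6 m and +12.7 m.

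In 40,000 simulated trials at 17 per arm, false wins for AIH rose from the nominal 2.5% to 3.4–4.5% in the second case and to 4.1–5.6% in the third. Analysing everyone left them at about 2.5%. All exclusion fractions and correlations here are assumed. Reversing the unequal fractions reverses the sign.

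**4. The sections side by side.** Outcome measures builds its denominators so that a person who drops out or is disqualified by an adverse event contributes up to that point. Duration excludes the data of anyone who misses a session, and a person who stops during the two weeks misses every later one. Both cannot apply to the same participant. Return after medical clearance is compatible with Duration only if no session was missed in the meantime.

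**The case against.** Several points on the other side stand.

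- **Hypertension and dysreflexia.** A reader might infer that the rule makes daily AIH look safer on these two outcomes. With invented counts, 6/34 v 2/34 is a relative risk of 3.0. Deleting three AIH participants whose event made them miss a session gives 3/31 v 2/34, or 1.65. That presupposes that the Duration sentence overrides the specific definitions in Outcome measures. The article does not say so, and Adverse event reporting separately runs from enrolment to the last follow-up visit. The supported statement is that the text is contradictory.
- **Certain bias.** A reader might infer that the efficacy comparison is biased. It can be, but identical exclusion in both arms gives zero bias under no effect. It would also be wrong to take a shift in one arm's mean for bias in the contrast. For example, if 20% are excluded who are 0.5 to 1 SD worse, 0.2 × 45 = 9 m to 0.2 × 90 = 18 m. The contrast shifts by that much only if the other arm loses nobody, or loses people at random. The contrast figures in the working, +5 to +13 m, are modest against the planned 100 m.
- **Excluded fractions.** Because (1 − p)^10 is convex, variation in miss risk between people lowers the excluded fraction at the same average p. The tabulated percentages are upper ends for each average rate. At 3%, Aim 2 power is still 0.79.
- **Return after clearance.** A participant may be cleared before the next session or during follow-up, and nothing says that a terminated session counts as missed. This is a tension, not a flat contradiction.

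One might also say that analysis populations belong in an analysis plan that is not shown. That does not answer the point, because the article states the rule outright and the rule also stops data collection.

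**Conclusion.** The concern holds in this form. The rule is an unqualified post-randomisation exclusion that treatment can influence, and nothing in the article offsets it for efficacy. It can bias the randomised comparison, in a direction and by an amount that the article does not allow one to determine.

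On safety, it contradicts the hypertension and dysreflexia definitions. For pain and spasticity, which have no protective wording, a literal reading could make daily AIH look safer if people with worse scores are the ones who miss sessions.

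The attrition allowance is fragile: under independent, equal-risk misses it is gone at 1.27% per session. The 18%, 26% and 40% figures depend on assumed rates of 2%, 3% and 5%. The finding does not depend on any particular rate.

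**What to change.** Replace the sentence under Duration so that randomised participants who miss treatment sessions continue to be invited to every scheduled assessment, unless they withdraw or are withdrawn from the study. This concerns assessment and analysis only, not whether or how treatment continues. Then state:

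- **Efficacy:** analyse by randomised group with all available data. Hypothesis 2 can use the mixed model already planned, which accommodates missing visits. Hypothesis 1 cannot borrow it: its planned Friedman analysis by ranks needs complete repeated measures. Name a method for the ordinal recovery score that compares arms and tolerates missing visits, for example an ordinal mixed model or a rank-based between-arm comparison.
- **Safety:** include everyone who had at least one session, with data up to dropout, for all four maladaptive outcomes.
- **Full attenders:** keep as a labelled sensitivity analysis.
- **Consistency:** reconcile Duration, Safety precautions and Outcome measures, including what counts as a missed session.

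The cost is a wording change, visits that are already in the schedule, and some dilution of the effect seen in full attenders. The trial began in January 2016 and restarted in January 2019. Assessments already forgone under the rule cannot be recovered, but data already collected from those participants can be restored to the analyses. The number affected should be reported by arm.
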